### Subjects of study

Caucasian women with lymphoedema who have undergone a prior mastectomy, tumorectomy or quadrantectomy and axillary lymphadenectomy. A sample size of 58 patients randomized in 1:1 ratio (29 per group) will be required.

### Inclusion criteria

• Women older than 18 years treated for unilateral breast cancer with ipsilateral axillary lymphadenectomy.

• Patients with ipsilateral lymphoedema with a limb volume difference of at least 200 ml compared to the lateral member.

• Patients who have finished treatment with radiotherapy and/or chemotherapy at least six months before the study begins.

• Informed consent must be signed

### Exclusion criteria

• Bilateral arm involvement.

• Malignant Lymphoedema of acute appearance (within the first three months postintervention)

• Patients with paralysis or previous vascular disorder in the affected arm.

• Patients with a major limitation of 30% or more in any of the arcs of movement of the ipsilateral shoulder.

• Patients with a contraindication for Manual Lymphatic Drainage (cellulite, deep venous thrombosis, heart failure, uncontrolled hypertension, renal impairment and radiodermatitis.

• Patients who have undergone rehabilitation within three months prior to recruitment.

### Treatment groups

#### Group A or Control Group

Ambulatory treatment is performed for one month. Specific exercises and prevention measures are taught. In the first four weeks, multilayer bandage is applied daily. Bandaging consists of a first layer of cotton (Velband) followed by protection at the points of support and a bandage of low elasticity (Comprilan) of different widths (six centimeters for the area of the hand and eight centimeters for the rest of the extremity).

The tailor-made sleeve for lymphoedema with a gauntlet without protection at the edges and with extension to the shoulder is applied for the first four weeks of treatment. The sleeve is used all day, and at night interruption is allowed. Later on, the patient will continue domiciliary treatment, performing specific exercises for 30 minutes twice a day without experiencing fatigue, and wearing the lymphoedema sleeve for at least 12 hours.

If after three months of treatment a satisfactory response is not achieved, an ambulatory treatment will be re-established for one month, and this time the experimental treatment (group B) will be used.

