**Methods:**

A randomized, controlled clinical trial in 58 women with post-mastectomy lymphoedema. The control group includes 29 patients with standard treatment (skin care, exercise and compression measures, bandages for one month and, subsequently, compression garnments). The experimental group includes 29 patients with standard treatment plus Manual Lymphatic Drainage. The therapy will be administered daily for four weeks and the patient's condition will be assessed one, three and six months after treatment.

The primary outcome parameter is volume reduction of the affected arm after treatment, expressed as a percentage. Secondary outcome parameters include: duration of lymphoedema reduction and improvement of the concomitant symptomatology (degree of pain, sensation of swelling and functional limitation in the affected extremity, subjective feeling of being physically less atractive and less feminine, difficulty looking at oneself naked and dissatisfaction with the corporal image).

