#### - Group B. Experimental group

Ambulatory treatment is carried out for one month. Specific exercises and prevention measures are taught. In the first four weeks, MLD is applied followed by a daily multilayer bandage. The bandage consists of a first layer of cotton (Velband) followed by protection at the points of support and a bandage of low elasticity (Comprilan) of different widths (six centimeters for the area of the hand and eight centimeters for the rest of the extremity). The tailor-made sleeve for lymphoedema with a gauntlet without protection at the edges and with extension to the shoulder is applied for the first four weeks of treatment. The sleeve is used all day, and at night interruption is allowed. Later on, the patient will continue domiciliary treatment, performing specific exercises for 30 minutes twice a day without experiencing fatigue, and wearing the lymphoedema sleeve for at least 12 hours.

If after three months of treatment a satisfactory response is not achieved, an ambulatory treatment will be re-established for one month, and this time the treatment corresponding to group A or control group will be applied.

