### Outcomes

#### Primary Outcome

Volume reduction of lymphoedema in the affected arm after treatment, expressed as a percentage. The condition is considered to be lymphoedema when there is a difference of at least 200 ml between the volume of the affected arm (measured by circometry and calculated using the formula of the truncated cone) and the volume of the contralateral arm. A response is considered to be good when a reduction of at least 20% of the volume is achieved after the treatment of lymphoedema in the affected extremity compared to baseline. These measurements will be performed at the beginning of the study, after the first and third month and after six months of follow-up. The volume difference has been used for the predetermination of the sample size.

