### Interventions and distribution of tasks

The rehabilitation physician's functions include:

1. Selection call: the physician determines whether the patient meets inclusion criteria and if so, she is randomized into a treatment group. He/she carries out a complete medical history (history and complete physical exam, taking measurements of both upper extremities for the calculation of lymphoedema volume). He/she explains and provides the informed consent and collects the signed copy. He/she gives the quality of life questionnaire to the patient, who will complete it before starting the outpatient treatment.

2. Week 2 of treatment: Examine the patient. Take measurements of the upper extremities. Rule out the existence of treatment-related side effects. Make the request for a lymphoedema garment. Collect the quality of life questionnaires.

3. Week 5 of treatment: Examine the patient. Take measurements of the upper extremities. Rule out the existence of treatment-related side effects. Check the sleeve. Give a compliance diary to the patient.

4. Week 12 of treatment: To examine Explore the patient. Ask about possible complications that may lead to withdrawal from the study. Take measurements of both upper extremities. If the response to the treatment is good, the patient will be encouraged to continue complying with treatment. The patient's diary is reviewed. A second quality of life questionnaire is provided. The treatment is continued at home. If the response to the treatment is poor, the patient is included again in an outpatient treatment for a month so that if the patient has previously received TH now he/she would be treated with TH + DL and if he/she has been previously treated with TH + DL now she would be treated with DL. The patient is examined at week 16. Measurements of the upper extremities are taken. The presence of treatment-related side effects is ruled out.

5. Week 18 of treatment: the patient is examined. Measurements of the upper extremities are taken. The presence of treatment-related side effects is ruled out. The sleeve is reviewed. A second quality of life questionnaire is delivered.

6. Final call: Week 24 of treatment: the patient is examined. The patient is asked about possible complications that may lead to withdrawal from the study. Measures are taken in both upper limbs. The sleeve is reviewed.

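### Response-driven re-treatment after week 12 gives some controls MLD, so the six-month intention-to-treat comparison does not estimate the long-term effect of MLD against standard care

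*Protocol article*

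**What the plan says.** All references are to the Protocol article.

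- **Re-treatment of controls.** If the response is unsatisfactory after three months, "an ambulatory treatment will be re-established for one month, and this time the experimental treatment (group B) will be used" (Group A or Control Group).
- **Re-treatment of MLD patients.** In the same situation, "this time the treatment corresponding to group A or control group will be applied" (Group B. Experimental group). The physician's task list words this differently: "if he/she has been previously treated with TH + DL now she would be treated with DL" (Interventions and distribution of tasks, item 4).
- **Timing.** At week 12 the task list puts the measurement before the decision: "Take measurements of both upper extremities. If the response to the treatment is good". For those re-treated, "The patient is examined at week 16", and volumes are taken again at weeks 18 and 24.
- **Outcome.** The primary outcome is the percentage reduction in volume after treatment, with measurements at baseline and "after the first and third month and after six months of follow-up" (Primary Outcome). The same section defines response: "A response is considered to be good when a reduction of at least 20% of the volume is achieved".
- **Long-term claims.** The aim at the end of the Background covers both short-term and long-term effectiveness of MLD. The Abstract adds: "Secondary outcome parameters include: duration of lymphoedema reduction".
- **Analysis population.** The Statistical analysis section uses intention to treat throughout; its only exception concerns withdrawal of treatment.

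**The concern.** From week 12 the randomised arms are no longer MLD plus standard care against standard care. They become MLD followed by the control regimen if the response is poor, against the control regimen followed by MLD if the response is poor. The re-treatment month is over by about week 16, so the six-month volume carries its effect.

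The Background presents permanence of the MLD effect as an open question, because earlier studies measured volume straight after MLD ended. Six months is the time point meant to go furthest towards an answer. If the difference narrows between three and six months, the MLD effect may have waned or the controls may have caught up after receiving MLD, and the planned comparison cannot tell these apart. A lasting benefit could then be reported as one that fades, and the Discussion links the provision of trained staff to whether MLD proves effective.

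**Working it through.** **Inputs from the protocol.** Mean reduction 5% (control) and 25% (MLD), SD 25%, alpha 0.05, power 0.80, 20 per group, 30% dropout, 29 per group (Sample Size). Good response means a reduction of at least 20% (Primary Outcome).

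**Assumptions not in the protocol.** Reductions are normally distributed, the planning values hold at week 12, the 20% rule is the re-treatment trigger, every poor responder accepts re-treatment, and dropout is unrelated to response. The re-treatment gains are also assumed.

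**Step 1: the plan's own figure.** n per group = 2(z_α + z_β)²(SD/Δ)². One-sided: 2 × (1.645 + 0.842)² × (25/20)² = 19.3, so 20; then 20/0.7 = 28.6, so 29. Both stated figures reproduce. Two-sided, the formula gives 24.5, so 25 (36 after dropout). Sidedness is not stated. That is a separate matter and does not affect what follows.

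**Step 2: share re-treated.**

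- Control: P(N(5, 25) < 20) = Φ(0.6) = 0.7257. Of 29 this is 21.0; of 20 completers, 14.5.
- MLD: P(N(25, 25) < 20) = Φ(−0.2) = 0.4207. Of 29 this is 12.2; of 20 completers, 8.4.

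**Step 3: effect on the six-month difference.** Let D0 be the difference there would have been without re-treatment, and gC and gM the mean gains at six months among re-treated controls and re-treated MLD patients. Then

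difference = D0 − 0.7257·gC + 0.4207·gM.

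The shift does not depend on D0, that is, on how far the original effect has waned.

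| gC, gM (points) | Shift | If D0 = 20 | If D0 = 10 |
|---|---|---|---|
| 25, 5 | −18.14 + 2.10 = −16.0 | 4.0 | −6.0 |
| 20, 0 | −14.5 | 5.5 | −4.5 |
| 20, 20 | −14.51 + 8.41 = −6.1 | 13.9 | 3.9 |
| 10, 10 | −3.1 | 16.9 | 6.9 |
| 5, 10 | −3.63 + 4.21 = +0.6 | 20.6 | 10.6 |

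The difference shrinks unless gM/gC is at least 0.7257/0.4207 = 1.72. With a laxer trigger of 10% (58% and 27% re-treated), the shifts run from −13.1 to −0.2. With 0% (42% and 16%), they run from −9.7 to −0.5.

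**Step 4: precision of a responder estimate at six months without re-treatment.** If week 12 reductions persist and nobody drops out, the shares are 1 − 0.7257 = 0.274 and 1 − 0.4207 = 0.579, a difference of 30.5 points. The 95% half-width is 1.96 × √[(0.274 × 0.726 + 0.579 × 0.421)/29] = 0.242. Exact enumeration of the uncorrected two-sided chi-square test with 29 per arm gives power 0.654. If the planned 30% dropout counts as non-response, the shares become 0.192 and 0.405, the half-width 0.229 and the power 0.423.

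**The case against.** Intention to treat after response-driven re-treatment is a legitimate comparison of the two initial assignments, each with its re-treatment rule. That stands: the analysis is not invalid, and re-treating patients who do badly is reasonable care. The protocol is also a condensed article, and the handling of measurements after a switch is commonly left to an analysis plan. But the point does not rest on missing detail. The switch, the intention-to-treat rule and the long-term aim are all written down, and together they do not fit.

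A reader might infer more than the document supports:

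- **That the main result is compromised.** The primary outcome is reduction after treatment. One month precedes any switch, and at week 12 the measurement is listed before the decision. The Primary Outcome section lists six months in the measurement schedule but does not make it the primary time point.
- **That a week 18 comparison is affected too.** Week 18 appears only as a visit in the physician's task list. The stated outcome times are one, three and six months.
- **That the six-month difference must shrink by a known amount.** The gains are assumed. The largest shifts give patients selected for poor response a mean gain of 20 to 25 points, and one scenario widens the difference.
- **That the trigger is undefined.** The treatment-group sections speak of a satisfactory response, but the week 12 entry speaks of a good one, and the Primary Outcome section defines good as at least 20%. Read together, the 20% rule is the natural trigger.
- **That re-treated MLD patients receive MLD again.** The task list says so literally, but the Group B section explicitly gives them the control regimen. This looks like a slip.

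**Conclusion.** The point holds for the six-month result only. That comparison is between two strategies with response-driven re-treatment. It does not estimate the long-term effectiveness of MLD, or the duration of its reduction, against standard care. This follows from the stated rules and needs no numerical assumption.

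The size is illustrative. About 73% of controls and 42% of MLD patients would be re-treated under the assumptions listed. Attenuation is likely, because more controls than MLD patients switch and the controls switch to MLD, but it is not certain. The shifts tried run from −16.0 to +0.6 points against a planned difference of 20.

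This should be fixed because a stated aim and a named secondary outcome depend on it. It is not more serious than that, because the after-treatment result is not at risk, and the three-month comparison is also sound provided the week 12 volume is taken before re-treatment starts.

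**What to change.** 1. Base the conclusion on MLD against standard care on volumes measured before the switch: end of treatment (about one month) as primary, and week 12 as the longest time point unaffected by re-treatment. State that the week 12 volume is recorded before the re-treatment decision.
2. Report six-month volumes by intention to treat as a comparison of strategies, with the number re-treated in each arm. Do not call the result the long-term effect of MLD against standard care.
3. Optionally, add the share of all randomised patients with at least 20% reduction at six months without re-treatment, as a supportive estimate with its confidence interval. It dichotomises a continuous outcome and is largely settled at week 12. Power is about 65% at best and about 42% with the planned dropout, so it should not carry the conclusion. The Efficacy analyses section already plans risk ratios and NNT.

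As a wording clean-up, name the 20% rule as the trigger in both treatment-group sections, and make the task list agree with the Group B section.

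The cost is wording and, if wanted, one extra analysis; no new data are needed and the re-treatment offer stays. The downside is a weaker six-month claim about MLD.

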#### - Group B. Experimental group

Ambulatory treatment is carried out for one month. Specific exercises and prevention measures are taught. In the first four weeks, MLD is applied followed by a daily multilayer bandage. The bandage consists of a first layer of cotton (Velband) followed by protection at the points of support and a bandage of low elasticity (Comprilan) of different widths (six centimeters for the area of the hand and eight centimeters for the rest of the extremity). The tailor-made sleeve for lymphoedema with a gauntlet without protection at the edges and with extension to the shoulder is applied for the first four weeks of treatment. The sleeve is used all day, and at night interruption is allowed. Later on, the patient will continue domiciliary treatment, performing specific exercises for 30 minutes twice a day without experiencing fatigue, and wearing the lymphoedema sleeve for at least 12 hours.

If after three months of treatment a satisfactory response is not achieved, an ambulatory treatment will be re-established for one month, and this time the treatment corresponding to group A or control group will be applied.

### Outcomes

#### Primary Outcome

Volume reduction of lymphoedema in the affected arm after treatment, expressed as a percentage. The condition is considered to be lymphoedema when there is a difference of at least 200 ml between the volume of the affected arm (measured by circometry and calculated using the formula of the truncated cone) and the volume of the contralateral arm. A response is considered to be good when a reduction of at least 20% of the volume is achieved after the treatment of lymphoedema in the affected extremity compared to baseline. These measurements will be performed at the beginning of the study, after the first and third month and after six months of follow-up. The volume difference has been used for the predetermination of the sample size.

#### Secondary Outcomes

The results of the Spanish validated quality of life questionnaires, EORTC QLQ-C30 version 2.0 for cancer in general and EORTC QLQ-BR23 specific for breast cancer, are used to assess the efficacy of the treatment, measuring the improvement of the lymphoedema concomitant symptomatology. Particularly, the items of the latter referring to the upper extremity (47, 48, 49) and to the corporal image (39, 40, 41, 42) are analyzed and the higher the score, the worse the result.

The secondary outcomes include:

• Degree of pain in the affected upper extremity

• Degree of sensation of swelling in the affected upper extremity

• Degree of functional limitation in this extremity

• Subjective feeling of being physically less atractive

• Subjective feeling of being less feminine

• Difficulty looking at oneself naked

• Dissatisfaction with the corporal image

### Statistical analysis

All patients included in the study will be analyzed and all the analyses will be performed in the "intention to treat" population, except those related to the withdrawal of treatment, which will be performed in the per-protocol population.

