### Sample Size

For the calculation of the sample size we make the following assumptions:

• The effect of the standard treatment on the control group will cause an average limb volume reduction of 5%.

• The effect of the treatment on the experimental group will cause an average limb volume reduction of 25%

• We also assume that the standard deviation will be similar in both groups and near to 25%. With this information and with an alpha risk of 0.05 and a power of 0.80, the calculation of the sample size is 20 patients in each group. Considering a 30% dropout rate in each group, the corrected sample size is 58 patients randomized in two groups of 29 patients each.

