#### Efficacy analyses

The analyses of the efficacy will be carried out using common measures such as mean and/or median ratio differences for the quantitative variables and risk ratios (relative risk) and NNT for the quantitative variables.

In all cases, the corresponding confidence intervals will be calculated.

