##### Safety Analyses

Side effects, withdrawal and/or complication rates will be studied in the same way as those described for the quantification of the efficacy in the case of qualitative variables. In all case analyses, the confidence intervals will be also calculated.

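### Withdrawal analyses are assigned to the per-protocol population, which in its usual sense leaves out the patients who withdrew

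*Protocol article*

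**What the plan says.** The Statistical analysis section of the protocol article sets the general rule: "All patients included in the study will be analyzed and all the analyses will be performed in the 'intention to treat' population". The same sentence then carves out a single exception: "except those related to the withdrawal of treatment, which will be performed in the per-protocol population".

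The Safety Analyses section names withdrawal as something to be quantified: "Side effects, withdrawal and/or complication rates will be studied in the same way as those described for the quantification of the efficacy". It points to the methods for qualitative variables and asks for confidence intervals. Under Efficacy analyses, the measures for such variables are evidently the risk ratio and the number needed to treat, although the text there reads "risk ratios (relative risk) and NNT for the quantitative variables", where qualitative appears to be meant.

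Under Interventions and distribution of tasks, the physician's week 12 visit includes the instruction "Ask about possible complications that may lead to withdrawal from the study", and the week 24 visit has the same question. The Sample Size section allows for losses: "Considering a 30% dropout rate in each group, the corrected sample size is 58 patients randomized in two groups of 29 patients each".

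The article does not say who belongs to the per-protocol population. No other section names all randomised patients as the denominator for withdrawal.

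**The concern.** A per-protocol set usually keeps the patients who completed treatment as planned. Those who withdrew from treatment are among the first to be left out. Comparing withdrawal rates within that set means selecting patients on the outcome not having happened, which distorts both the numerator and the denominator.

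The comparison matters in this trial. The experimental arm adds manual lymphatic drainage to the daily bandaging for four weeks, and the Background puts a session at 45 to 60 minutes, so unequal withdrawal is plausible. The Discussion also criticises earlier trials for rarely analysing loss to follow-up. A rule that removes withdrawals from their own analysis would weaken this trial on a related point.

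**Working it through.** **Inputs**

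- Before dropout: 20 per group, from alpha 0.05, power 0.80, means of 5% and 25%, SD 25% (Sample Size).
- Dropout allowance: 30% in each group (Sample Size).
- Randomised: 29 per group, 58 in total (Sample Size; Subjects of study).
- Population for withdrawal analyses: per-protocol, undefined (Statistical analysis).
- Assumption made here: the 30% dropout allowance stands in for the treatment-withdrawal rate. The article gives no withdrawal rate.

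**Step 1. Reproduce the plan's figures.**

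n per group = 2 × (z_alpha + z_power)² × (SD / difference)². With one-sided alpha 0.05 this is 2 × (1.645 + 0.842)² × (25/20)² = 19.3, rounded up to 20, which matches. (Two-sided alpha gives 25. The article does not state sidedness. That is a separate matter and does not bear on this point.)

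Inflation for dropout: 20 / (1 − 0.30) = 28.6, rounded up to 29 per group, and 2 × 29 = 58. Both match.

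**Step 2. Expected withdrawals per arm, under the assumption.**

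0.30 × 29 = 8.7, say 9, which leaves 29 − 9 = 20.

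**Step 3. The same trial under two denominators.**

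| Population | Withdrawals per arm | Rate (exact 95% CI) | Risk ratio |
|---|---|---|---|
| All randomised | 9/29 | 31.0% (15.3% to 50.8%) | 1.0 |
| Per-protocol, all withdrawals excluded | 0/20 | 0% (0% to 16.8%) | 0/0, undefined |

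In the second row the risk difference is zero whatever happened in the trial, so the number needed to treat (1 / risk difference) cannot be calculated either.

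**Step 4. Unequal withdrawal (assumed figures, for illustration).**

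Take 4 of 29 in one arm and 13 of 29 in the other.

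- All randomised: 4/29 = 13.8% and 13/29 = 44.8%; risk ratio 13/4 = 3.25.
- Per-protocol with withdrawals excluded: 0/25 and 0/16. The difference disappears.

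**Step 5. A looser per-protocol definition.**

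Suppose the set needs only a minimum amount of treatment, so that k of the 9 withdrawals are excluded and the later ones stay in. The observed rate is (9 − k) / (29 − k):

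- k = 3: 6/26 = 23.1%
- k = 5: 4/24 = 16.7%
- k = 9: 0/20 = 0%

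The rate falls short of 31.0% for any k above zero. The result therefore runs from an understated rate to no events at all, depending on a definition that the article does not give.

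**The case against.** The strongest reply is that the clause is ambiguous. It speaks of analyses connected with withdrawal of treatment, not of withdrawal rates. The authors may have meant a per-protocol efficacy analysis to deal with patients who stopped. Withdrawal rates would then stay under the intention-to-treat default, and the Safety Analyses section, which ties them to the efficacy methods, gives this reading some support. It does not settle the matter. That section most naturally concerns effect measures, and the exception clause is the only statement that links withdrawal to a population. Under this reading the sentence still needs rewriting, because it does not say what was meant.

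The other objections limit the size of the point, and they stand:

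- Per-protocol is undefined, and a condensed article may leave its definition to the full protocol. A reader might infer that withdrawal rates must come out at zero. That holds only if every patient who withdrew is excluded.
- The 30% is a dropout allowance. A patient can stop treatment and still be measured, or complete the four weeks and be lost later. The figure of 9 of 29 is an illustration, not a forecast by the protocol.
- A reader might infer that tolerability cannot be compared at all. The documents do not support this: the exception covers withdrawal only, and side effects and complications remain under intention to treat.
- A reader might infer that unequal dropout would go unseen. That is also too strong, because losses per arm can be counted from the 29 randomised. The planned risk ratio and its interval are what would be wrong.
- A reader might infer that poor responders would vanish as withdrawals. The Treatment groups section sends them at three months to a further month of treatment within the study. Whether they stay in the per-protocol set is not stated.

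**Conclusion.** The point holds as a fault in one clause. Read as written, and with per-protocol in its usual sense, the plan assigns the withdrawal comparison to a set from which most or all of the withdrawals have been removed. With 30% taken as the withdrawal rate, 31% per arm becomes 0% and the risk ratio is undefined; a looser definition gives an understated rate. Both results depend on that assumed rate and on a per-protocol definition that the article does not supply.

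This should be fixed, but it does not threaten the trial's main conclusions. Withdrawal appears only as a safety outcome, and the populations for the primary and secondary efficacy outcomes are unaffected.

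**What to change.** Delete the exception clause or replace it. Suitable wording would be: withdrawal from treatment is compared by assigned arm in all randomised patients, with the reason and the time of each withdrawal reported. If a per-protocol set is wanted, define it, including how it treats patients who enter the further month of treatment after a poor response at three months, and use it only for a supporting efficacy analysis. Leave the intention-to-treat default as it is.

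The cost is one sentence in the Statistical analysis section, plus a definition if the per-protocol set is kept. The number randomised per arm is known, and complications that may lead to withdrawal are already asked about at weeks 12 and 24. The date and the other reasons for stopping need only be recorded when a patient withdraws.
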